##### Secondary objectives

To evaluate the PK profile up to 6 months of each single bNAb administered, at different doses within 96 hours of birth in breastfeeding HIV exposed neonates born without HIV (arms 1 through 5).To evaluate the PK profile up to 3 months of bNAbs administered in combination, at different doses within 96 hours of birth in breastfeeding exposed neonates without HIV (arm 6).To evaluate the PK profile up to 6 months of each bNAb, administered in combination, in breastfeeding exposed neonates without HIV infants after a second administration at 3 months (arms 6/6b).To assess safety (AE) up to 6 months after each single bNAb (arms 1 to 5), up to 3 months after the first combined bNAbs administration (arm 6) and up to 6 months after the second administration of the combined bNAbs (arm 6b).

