#### Statistical methods

The statistical analyses of the PedMAb phase I trial will be performed, unblinded as to study arm, on the “safety analysis dataset” including infants who will have received at least one dose of the randomized bNAb (alone or in combination) and who have either presented a SAE grade 3–4 during the first 28 days following first or second bNAb administration or who have completed the same follow-up with safety assessment.

The analyses will be also performed according to the per-protocol (PP) principle. The PP analysis dataset will comprise infants who have received the expected dose(s) of the randomized bNAb (alone or in combination) and who have completed all their follow-up visits (6 months) since the first or second bNAb administration.

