#### Secondary analyses on secondary endpoints

AEs rates, expressed as number of events divided by number of person-days of follow-up and calculated by univariate Poisson regression, will be also estimated among enrolled neonates.

Pharmacokinetic parameters will be estimated by a non-compartmental analysis (NCA) performed using WinNonlin® version 8.0 (Certara, St. Louis, MO, USA) applied on data collected from neonates who completed the study. The primary PK endpoints will be: clearance, maximum plasma concentration (C_max_) and area under the concentration–time curve (AUC) from time zero to the last quantifiable time point (AUClast). C_max_ values will be compared with those at baseline (pre-administration of bNAbs) using the Wilcoxon signed-rank test. Bioequivalence between study arms will be assessed using the geometric mean ratio (GMR) and 90% confidence interval (90% CI) of AUClast and C_max_. The conventional bioequivalence criterion of 0.80 will be used.

The other endpoints of the trials will be summarized with descriptive analyses; they will be described according to the study arm and, if assessable, by month of follow-up until a maximum of 6 months since first or second bNAbs administration, using means with standard deviations or medians with interquartile ranges or ranges or 95%CI for quantitative variables, and proportions with their 95% CI for qualitative or categorical variables. Non-parametric tests that will be considered to test changes in continuous measures during follow-up are: Wilcoxon signed-rank test or Friedman test.

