#### Toxicity management second administration – Study arm 6b

A second bNAbs administration will occur in arm 6b and should be provided according to the following criteria:In case of Grade 3 toxicities after the first bNAbs administration (regardless of their relationship to study product), the second dose should not be administered until after consultation with the study investigators AND improvement of the event to < Grade 3. After approval by the study investigators and the ISMC, the second administration may occur. If the event persists, no further administrations may occur.In case of Grade 4 toxicities considered as not related or possibly or probably not related, the second administration may occur after improvement to < Grade 3 and consultation with the study investigators and the ISMC. If the event persists, no further administrations may occur.

Subsequent administration should not occurIn case of any Grade 4 toxicities considered as possibly, probably, or definitely related to study product,.In case the infant has documented or suspected serious medical or immediate life-threatening condition at the time of the planned second bNAb administration.In case the infant is admitted in ICU or high care requiring supplemental oxygen at time of planned second bNAbs administration.In case an infant is determined to have acquired HIV after the first bNAb administration orIn the case of an infant who has stopped breastfeeding (before the second dose).

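### Limiting the non-compartmental PK analysis to study completers discards usable PK data, including first-dose profiles in arm 6; the supplementary per-protocol set has a related, smaller problem

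*Protocol article*

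**What the plan says.** **PK population.** Under *Secondary analyses on secondary endpoints*, the non-compartmental analysis is "applied on data collected from neonates who completed the study". The article names no other PK population. The main PK endpoints there are clearance, Cmax and AUC "from time zero to the last quantifiable time point (AUClast"). Arms are compared by geometric mean ratios of AUClast and Cmax with 90% intervals.

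**PK horizon.** *Secondary objectives* sets 6 months for arms 1 to 5. For the first combined dose (arm 6) the aim is "To evaluate the PK profile up to 3 months of bNAbs administered in combination". In Table 5 the end-of-trial visit for arm 6/6b is 6 months after the second dose, at month 9 after delivery.

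**Analysis sets.** *Statistical methods* bases the main analysis on a safety dataset of "infants who will have received at least one dose of the randomized bNAb" and who either had a qualifying event within 28 days or completed that follow-up. It then adds: "The analyses will be also performed according to the per-protocol (PP) principle". The per-protocol set needs two things: the infants must have received the doses expected for their allocation, and they must be infants "who have completed all their follow-up visits (6 months) since the first or second bNAb administration".

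**Withheld second dose.** *Toxicity management second administration – Study arm 6b* bars the second dose after a related Grade 4 toxicity. For a Grade 3 or an unrelated Grade 4 event it says: "If the event persists, no further administrations may occur". It also bars the dose for serious illness, intensive or high care needing oxygen, HIV acquisition, or stopped breastfeeding.

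**The concern.** The completion rule asks for more follow-up than the PK quantities need. Cmax is fixed by early samples. An AUC to a given time needs samples only up to that time. First-dose PK in arm 6 is defined over the 3 months before the second dose, yet an infant must be followed for a further 6 months before that profile may be used. With 8 infants per arm, each profile set aside costs visible precision. If infants who leave differ from those who stay, completers may also give a biased picture.

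The per-protocol set has a milder form of the same fault. It applies a 6-month condition and a full-dosing condition to a primary endpoint that needs 28 days. In arm 6/6b, an infant managed exactly as the toxicity section directs can fail the dosing condition because of the outcome being counted. In any arm, an infant who dies or leaves because of an adverse event fails the follow-up condition.

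**Working it through.** **1. The plan's own figure.** *Sample size calculation* gives a target of 6 per arm, 25% loss and 8 enrolled. 6 / (1 − 0.25) = 8 per arm, and 8 × 6 groups of infants = 48. Both reproduce. Conversely, 8 × 0.75 = 6 remain.

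**2. Follow-up needed against follow-up required.**

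| Quantity | Data needed | Required by the completion rule |
|---|---|---|
| Cmax, any arm | samples around the peak | 6 months after the last dose |
| First-dose PK, arm 6 | up to month 3 | month 9 (3 + 6) after delivery |
| Clearance, half-life | adequate terminal phase | 6 months after the last dose |

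Take an arm 6 infant lost at month 5 after birth. The first-dose profile to day 84 is complete, and about two months of second-dose data exist. As written, none of it enters the analysis. This assumes that PK samples were taken at the scheduled visits; the article lists dried blood spots for PK, but its condensed visit tables show no PK rows.

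**3. Precision of a mean log PK parameter.** The 95% half-width in SD units is t(0.975, n − 1) / √n.
- n = 8: 2.365 / 2.828 = 0.836
- n = 7: 2.447 / 2.646 = 0.925, ratio 0.925 / 0.836 = 1.11
- n = 6: 2.571 / 2.449 = 1.049, ratio 1.049 / 0.836 = 1.26 (1.255 unrounded)

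**4. Precision of the comparison the plan specifies.** For a 90% interval of a geometric mean ratio between two independent arms with common variance, the log-scale half-width is t(0.95, 2n − 2) × √(2/n).
- n = 8 per arm: 1.761 × 0.500 = 0.881
- n = 6 per arm: 1.812 × 0.577 = 1.046, ratio 1.046 / 0.881 = 1.19

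So at the full allowance the widening is up to 26% for a single mean and about 19% for the ratio. With one infant lost, the single-mean figure is about 11%.

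**5. The per-protocol set in arm 6/6b.** Suppose one infant has a related Grade 4 event within 28 days of the first dose, completes the day 28 assessment and receives no second dose. Exact 95% intervals are:
- safety dataset: 1/8 = 12.5% (0.3% to 52.7%)
- per protocol, if both doses count as expected: 0/7 = 0% (0% to 41.0%)

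The infant leaves numerator and denominator together. Exclusions can also work the other way: if that infant stayed in and two event-free infants were lost, 1/8 would become 1/6 = 16.7%.

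**The case against.** **On PK.** Six per arm is the plan's own target, and *Missing data/loss to follow-up* expects little loss, so 25% is an allowance and not a forecast. Restoring 8 also assumes that every lost infant has a usable profile. AUClast from a shortened profile is not comparable with one from a full profile, which gives some reason to prefer completers. Detailed evaluability rules usually sit in a statistical analysis plan. All of this limits the size of the point. It does not remove it, because the completion restriction is a rule that the article itself states. Comparability is better secured by a common AUC interval than by dropping infants.

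**On the per-protocol set.** It is supplementary. The main safety dataset can keep an infant whose second dose was withheld, and *Descriptive and univariate analyses* promises to use all available safety data. Neither arm progression nor the pausing triggers use the per-protocol set. The example event would itself trigger a pause and a request for DSMB review. All of this stands.

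**Stronger readings.** A reader might infer that the trial's safety proportion is biased downward by construction. The documents do not support that:
- A withheld second dose can affect only the 8 infants of arm 6/6b.
- A Grade 3 event that improves may still be followed by the second dose, so that infant can remain.
- Event-free infants lost to follow-up, or who stop breastfeeding, push the proportion upward when excluded.

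Nor is it certain that every infant with a withheld dose leaves the sets. The article does not say whether a barred dose is still an expected one, how the wording about first or second administration applies to such an infant, or whether an infant who remains in follow-up has completed the study.

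**Conclusion.** The point holds, chiefly for PK. As written, the completion rule discards usable Cmax and AUC data from any infant who leaves early. For an arm 6 infant lost after month 3, it discards the whole first-dose profile that the objective asks for. The cost is at most about 26% in the width of a 95% interval for a log-mean and about 19% for the planned 90% ratio interval. These figures assume that the 25% allowance, stated for the safety dataset, also describes study completion, that both lost infants have usable samples, and that the SD is unchanged. Smaller losses cost less.

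The per-protocol problem is secondary. It can remove outcome-related cases from a supplementary table, by withheld doses in arm 6/6b only and by death or AE-related dropout in any arm. The main safety estimate survives, and the net direction of bias over all exclusions is not fixed. This is a should-change point, and wording suffices.

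**What to change.** **PK set** (*Secondary analyses on secondary endpoints*). Replace the completion condition with all dosed infants who have evaluable post-dose concentrations, defined separately for each dose period. Set evaluability by parameter: Cmax and AUC over a common interval from the samples available; clearance and half-life only where the terminal phase is adequate. Report the number of infants behind each parameter.

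**Per-protocol set** (*Statistical methods*). For the 28-day endpoint, define it by dose period: correct product and planned dose received for that period, with assessment to day 28 or an earlier event. State that a dose withheld under the protocol's own rules is not a deviation.

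**Cost.** Wording changes in two sections, slightly more PK data handling, and sample sizes that differ between parameters. No visit or infant is added, and the dosing and withholding rules are untouched.

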#### Descriptive and univariate analyses

All the available safety data of each participant will be considered in the analyses; these data will be classified as severity (grade), expectedness, and potential relatedness (causality) to the study intervention. Descriptive analyses will be performed according to the study arm and the endpoints will be summarized using means with standard deviations or medians with interquartile ranges or ranges or 95% confidence intervals (CI) for quantitative variables, and proportions with their 95% CI for qualitative or categorical variables; CIs will be calculated using the exact method.

Given the small sample size of the study arms, there will be no statistical power for a formal test of differences between study arms with respect to safety. The analyses will check for clinically relevant differences in the main baseline maternal and infant characteristics between the following study arms: 2 vs 3, 4 vs 5, 6 vs 3 and 5; the presence of relevant imbalances in these characteristics among arms will be eventually tested by calculating differences [between means (standardised effect size) or proportions] with the corresponding 95% confidence intervals.

#### Primary analysis on primary endpoint

The primary endpoint of each step is the proportion of neonates who develop at least one ≥ 1 Grade 3 adverse events (AE) possibly, probably or definitely related to each bNAb that occurred within 28 days after a first or a second dose of bNAbs administration (alone or in combination). The primary endpoint will be described according to the study arm, using proportions with the corresponding 95% CI.

#### Secondary analyses on secondary endpoints

AEs rates, expressed as number of events divided by number of person-days of follow-up and calculated by univariate Poisson regression, will be also estimated among enrolled neonates.

Pharmacokinetic parameters will be estimated by a non-compartmental analysis (NCA) performed using WinNonlin® version 8.0 (Certara, St. Louis, MO, USA) applied on data collected from neonates who completed the study. The primary PK endpoints will be: clearance, maximum plasma concentration (C_max_) and area under the concentration–time curve (AUC) from time zero to the last quantifiable time point (AUClast). C_max_ values will be compared with those at baseline (pre-administration of bNAbs) using the Wilcoxon signed-rank test. Bioequivalence between study arms will be assessed using the geometric mean ratio (GMR) and 90% confidence interval (90% CI) of AUClast and C_max_. The conventional bioequivalence criterion of 0.80 will be used.

The other endpoints of the trials will be summarized with descriptive analyses; they will be described according to the study arm and, if assessable, by month of follow-up until a maximum of 6 months since first or second bNAbs administration, using means with standard deviations or medians with interquartile ranges or ranges or 95%CI for quantitative variables, and proportions with their 95% CI for qualitative or categorical variables. Non-parametric tests that will be considered to test changes in continuous measures during follow-up are: Wilcoxon signed-rank test or Friedman test.

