**Description of Arms**					
	**N**	**Study product**	**Dose (mg/Kg)**	**Time (from birth)**	**Recruitment**
**Arm 1:**	8	CAP256V2LS	5	< 96 h	Sequential
**Arm 2:**	8	CAP256V2LS	10	< 96 h	Randomized
**Arm 3:**	8	CAP256V2LS	20	< 96 h	Randomized
**Arm 4:**	8	VRC07-523LS	20	< 96 h	Randomized
**Arm 5**	8	VRC07-523LS	30	< 96 h	Randomized
	**N**	**Study product**	**Dose (mg)**	**Time (from birth)**	**Recruitment**
**Arm 6**	8	CAP256V2LS + VRC07-523LS	60 + 90	< 96 h	Sequential
**Arm 6b**		CAP256V2LS + VRC07-523LS	120 + 120	3 months (12 weeks)	Same infants of arm 6

Based on emerging safety data of arms 1 to 5 [11] and PK (to be published), which were adjudicated by the internal study safety committee (ISSC), independent (external) safety medical committee (ISMC) and the Data Safety and Monitoring Board (DSMB), arm 6/6b includes a fixed dose of each antibody at each time point. Furthermore, the discussions confirmed that it would be best if the second doses were administered at 12 weeks (Table 2).

**Table 2 Tab2:** summarizes the step wise proceeding of the trial according to safety data

**Step 1**		Product* for dose 1	Dose 1	Timing for dose 1	Product for dose 2		Dose 2	Timing for dose 2
Arm 1:		CAP256V2LS	5 mg/kg	0- < 96 h	No second dose			

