##### Primary endpoint

The primary endpoint, applying to all the primary objectives, is the proportion of participants who develop at least one ≥ Grade 3 AE, including local and systemic reactions, lab toxicities, and/or clinical events, that is possibly, probably or definitely related to each bNAb any time from the first day of study product administration through further 28 days following bNAb(s) administration (all arms).

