##### Secondary endpoints

PK curve of each single bNAb.Clearance, C_max_, area under the curve (AUC) and elimination half-life of each single bNAb.Frequency/proportion of children above the target bNAb plasma concentration (IC80) determined by in vitro studies for each bNAb.Frequency of participants with any type of AE including local and systemic reactions, laboratory toxicities, and/or clinical events, any time from the first day of study product administration up to 6 months after each single or combined bNabs administration.Frequency/proportion of participants who develop at least 1 AE including local and systemic reactions, laboratory toxicities, and/or clinical events, any time from the first day of study product administration up to 6 months after each single or after the combined second bNabs administration.Frequency/proportion of new HIV-1 infection among neonates/infants.

The exploratory objectives and endpoints have been omitted in this paper for brevity.

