### Monitoring

#### Safety monitoring

The 2015 South African operational guidelines on Ministerial consent for non-therapeutic health research with minors will be followed. We will categorise this study as non-therapeutic research because this is a phase I dose-finding, safety and PK study; we do not know whether the interventions, at the doses and intervals tested, will have therapeutic benefit. The following conditions will be applied:Condition 1: All consent will be provided by one or both parent/guardian who is the main person looking after the child. Consent procedures will follow GCP procedures, i.e. information sheets will be translated in vernacular language and routine care will not be affected by non-participation.Condition 2: The research may carry a risk as CAP256V2LS has not been tested in an infant population; however, CAP256V2LS is an antibody that was specifically derived from a South African adult patient; it specifically targets the strain of HIV pervasive in southern Africa and is highly potent. The trial with CAP256V2LS is initiated with available adult safety data of CAPRISA 012B [13]. Additionally, children will be closely monitored to ensure safety and document reactogenicity and adverse events.

Babies will be observed for a minimum of 2 up to 4 h after the first antibody dose and for at least an hour after the second antibody dose and will be reviewed face-to-face at days 1, 3, 14 and 28 post-delivery, then monthly up to month 6 post-delivery for babies receiving a single administration and up to months 3 for babies receiving the first bNAb administration and for additional 6 months post second bNAb administration for babies receiving two administrations. Additionally, study doctors and nurses will be available telephonically and in-person 24/7, to receive any calls or to see mothers and their babies face-to-face, in between these scheduled visit time points.

The first antibody dose will be given in a hospital setting (either within the RK Khan hospital or at the clinical research site which is located on the hospital precinct) to ensure close proximity to intensive care unit facilities and access to more than one paediatrician and nurses.

Furthermore, the Chatsworth CRS has community liaison staff, which would also be available in the community, directly or through the community advisory board to provide any support to mothers and their babies and to facilitate their access to immediate health care.

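### The secondary proportion with at least one AE covers about 6 months in arms 1-5 but about 9 months and two doses in arm 6/6b, and the whole-follow-up AE rate dilutes any effect confined to the 28 days after a dose

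*Protocol article*

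**What the plan says.** All references are to the protocol article.

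- **Secondary endpoints.** The proportion of infants with at least one AE is counted "any time from the first day of study product administration up to 6 months after each single or after the combined second bNabs administration".
- **Safety monitoring.** Scheduled review runs "then monthly up to month 6 post-delivery for babies receiving a single administration". For arm 6/6b it runs for 3 months after the first administration and "for additional 6 months post second bNAb administration for babies receiving two administrations". The text with Table 1 places the second administration: "it would be best if the second doses were administered at 12 weeks". Table 5 ends at month 9 after delivery.
- **Secondary objectives.** Safety is to be assessed up to 6 months after a single antibody (arms 1-5), up to 3 months after the first combined administration (arm 6), and up to 6 months after the second (arm 6b). The objective thus keeps the two combined-dose periods apart.
- **Secondary analyses on secondary endpoints.** The plan adds "AEs rates, expressed as number of events divided by number of person-days of follow-up and calculated by univariate Poisson regression", with no time window or time term. The remaining endpoints are described by arm and, "if assessable, by month of follow-up until a maximum of 6 months since first or second bNAbs administration".
- **Primary endpoint.** It is limited to related events of Grade 3 or higher, "any time from the first day of study product administration through further 28 days following bNAb(s) administration".
- **Sample size calculation; Descriptive and univariate analyses.** Comparing safety between arms is not an objective, and no formal between-arm safety test is planned.

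**The concern.** There are two separate problems.

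The first is the window of the proportion. The chance of at least one AE rises with time observed. An endpoint that stops at 6 months in five arms and at about 9 months in the sixth will be higher in the sixth even if the products do nothing. It also merges the two periods that the secondary objective separates, so an event after the first combined dose cannot be told from one after the second.

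The second is dilution in the rate. One events-per-person-day figure over all follow-up averages the 28 days after a dose with months in which a short-lived reaction is no longer expected. The 28-day windows also make up a different share of person-time in arm 6/6b than in arms 1-5, so the same toxicity gives a different figure in each.

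What is at stake is the reading of the secondary safety tables. AEs of Grade 1-2, and AEs judged unrelated, appear only there and not in the primary endpoint. With 8 infants per arm and no test, readers will rely on the descriptive figures. The article itself plans to check baseline balance of arm 6 against arms 3 and 5, which suggests that those arms will be looked at together.

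**Working it through.** The article gives no figure for AE rates or for this proportion, so there is no stated value to reproduce.

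**Inputs from the article**

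- Arms 1-5: one dose, 6 months, taken as 182 days.
- Arm 6/6b: second dose at 12 weeks = 84 days, then 6 months. 84 + 182 = 266 days.
- Ratio of follow-up: 266/182 = 1.46.
- 8 infants per arm.

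**Assumptions, not in the article**

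- Background rate *m* from 0.02 to 1.0 AE per infant-month, with 30.4 days per month.
- Complete follow-up and no product effect, except in step 3.

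**Step 1: proportion with at least one AE, constant rate equal in all arms**

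P = 1 − exp(−*m* × T/30.4). For *m* = 0.1:

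- Arms 1-5: 1 − exp(−0.1 × 182/30.4) = 45.0%
- Arm 6/6b: 1 − exp(−0.1 × 266/30.4) = 58.3%

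| AE per infant-month (assumed) | Arms 1-5 | Arm 6/6b | Difference (points) |
|---|---|---|---|
| 0.02 | 11.3% | 16.1% | 4.8 |
| 0.05 | 25.9% | 35.4% | 9.6 |
| 0.1 | 45.0% | 58.3% | 13.3 |
| 0.2 | 69.8% | 82.6% | 12.8 |
| 0.5 | 95.0% | 98.7% | 3.8 |
| 1.0 | 99.7% | 100% | under 1 |

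(Differences are from unrounded values.) The largest possible gap is 13.9 points (56.1% against 69.9%, at about 0.137 per infant-month). That is 8 × 0.139 = 1.1 infants in an arm of 8.

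**Step 2: events per person-day, no product effect**

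- Constant background: the expected rate does not depend on T, so the ratio of arm 6/6b to arms 1-5 is 1.00.
- Background that changes with age: let the last 84 days in arm 6/6b run at *k* times the earlier rate. The ratio is (182 + 84*k*)/266, which gives 0.84, 0.92, 1.16 and 1.32 for *k* = 0.5, 0.75, 1.5 and 2. The article gives no value for *k*.

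**Step 3: dilution of an effect confined to 28 days after each dose**

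Share of person-time in those windows: 28/182 = 15% in arms 1-5 and 56/266 = 21% in arm 6/6b. For a true rate ratio R inside the window and 1 outside it:

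- Arms 1-5: (28R + 154)/182
- Arm 6/6b: (56R + 210)/266

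| True ratio in window | Seen in arms 1-5 | Seen in arm 6/6b |
|---|---|---|
| 2 | 1.15 | 1.21 |
| 3 | 1.31 | 1.42 |
| 5 | 1.62 | 1.84 |

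**Step 4: the same quantities in common windows**

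At 0.1 AE per infant-month, any 28-day window gives 1 − exp(−0.1 × 28/30.4) = 8.8% in every arm. A rate ratio of 2 confined to 28 days reads as 2 in its own window.

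**The case against.** The case against giving this much weight has four parts.

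1. **Rates already correct for length.** A reader might infer that unequal follow-up by itself makes the AE rates differ between arms. It does not: person-days are the denominator, and step 2 gives 1.00 under a constant background. A spurious difference in rates needs a background that changes with age. That is plausible in infants, but the article gives no figure for it. This objection stands in full.
2. **Early toxicity is looked at elsewhere.** A reader might infer that toxicity close to dosing is lost. The primary endpoint isolates 28 days after administration, the day-28 safety reviews do the same, and all AEs are classified by severity and relatedness. This stands for related events of Grade 3 or higher. It does not restore the 28-day window in the planned summaries of milder or unrelated events.
3. **Dose-anchored, by-month description is planned.** It is, but only if assessable. It is stated for the other endpoints, separately from the Poisson rate, and it leaves the cumulative window in the endpoint definition unchanged. This stands in part.
4. **No between-arm comparison is planned.** A reader might infer that the combination will be judged against the single antibodies on this table. The article does not say so: it excludes between-arm safety comparison from its objectives, and the sentence on Poisson rates does not state that they are given by arm. No planned decision rests on these figures. This stands, and it limits the consequence to informal reading.

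On size, the gap is near its maximum only for mid-range AE rates. The endpoint counts any AE, including local reactions and laboratory toxicities, so most infants may have one and the gap may be small. Sampling error is also larger than the gap: the exact 95% interval for 4 of 8 is roughly 16% to 84%.

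Table layout is commonly left to the analysis plan, which is not shown. The window of this endpoint, however, is fixed in the article.

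**Conclusion.** The point holds in limited form and is minor. As defined, the proportion with at least one AE is not comparable across arms: it covers about 182 days and one dose in arms 1-5, and about 266 days and two doses in arm 6/6b. It also merges periods that the secondary objective separates. With equal constant rates and no product effect, the gap is at most about 14 points, roughly one infant in 8, and it falls to about 5 points or less when AEs are rare (0.02 per infant-month) or nearly universal (0.5 or more).

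The whole-follow-up rate is unbiased by follow-up length alone, but it shrinks a 28-day doubling to 1.15 or 1.21. The follow-up lengths come from the article; the background rates and rate ratios are assumptions. The primary endpoint and the stated dose-progression reviews are not affected.

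**What to change.** Report AE proportions and rates by arm in windows anchored to each dose:

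- all arms: days 0-28 and days 29-84 after the first dose;
- arms 1-5: day 85 to 6 months;
- arm 6b: days 0-28, and day 29 to 6 months, after the second dose.

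Reword the endpoint so that the periods after the first and second combined administrations are separate, as in the secondary objective. If a cumulative 9-month figure is kept for arm 6/6b, label it with its window and do not set it beside the 6-month figures as comparable.

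The change uses data already scheduled for collection and leaves treatment, visits and sample size as they are. The cost is a few more table rows, with fewer events and wider intervals in each window.
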